### Inclusion and exclusion criteria

Eligible adolescents from the assigned schools will be asked to take part in the study. There are only two criteria for inclusion in the study: Participants must be aged between 11 and 14 years and in the 6th or 7th grade. We chose this age group because epidemiological data show that the end of childhood and the beginning of adolescence represents the period with the highest risk of onset of NSSI [22]. Accordingly, the first rise in incidence rates can be determined around the age of 14 years. Based on the rationale of universal prevention, a program should start before this period, keeping in mind that a universal prevention approach should start before a disorder develops [23]. Likewise, only two exclusion criteria will be applied: lack of informed consent from the adolescents or their relatives, and currently receiving individual psychotherapy because of a mental disorder. If participants report being in individual psychotherapy, to avoid stigmatization, they will still attend the training together with their classmates, and their data will be collected but saved separately. Thus, these participants will still be able to see information about their results, but these results will not be included in the data analysis. This procedure was chosen due to potential confounding effects between individual psychotherapy and the prevention program.

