### Sample size

The primary endpoint is the incidence of NSSI measured by the dichotomized DSHI-9 at T3. We assume an incidence rate (newly detected cases in the last 12 months) of 2.31% in the control group and 0% in the treatment group. This assumption is based on data from a longitudinal study by Baetens et al. [64], which reported a prevalence of 3% in the control group at age 12–13 years and a prevalence of 5.31% later at age 14–15 years. We hope that due to our prevention program, no new cases will occur in the treatment group and assume a stable prevalence rate of 3%. In the active control group, an increase from 2.31 to 5.31% in 1 year can be assumed based on the data of Baetens [64].

To account for the need for cluster randomization in our study, we need to calculate an intraclass correlation coefficient (ICC). We assume an ICC of 0.015. As there was no ICC available for NSSI, this assumption is based on data from two studies of binge drinking behavior in adolescents [65, 66]. Comparability between NSSI and binge drinking can be expected, as both represent maladaptive strategies for coping with one’s own feelings or for dealing with personal stress.

We plan to recruit 160 pupils per school (four classes per grade, 6th and 7th grade (age 11–14 years)). A two-sided unpooled *z*-test for cluster-randomized studies will be used to test the null hypothesis of equal proportions. A sample size of 160 pupils per school and eight schools per group yields a power of 80% to detect a difference between the proportions of 2.31%. The significance level will be set at 5%. Including a dropout rate of 20%, 200 pupils per school and a total number of 3200 pupils need to be recruited. The sample size was estimated using PASS 15.05.

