### Limitations

Despite the mentioned advantages, potential limitations of the study design should be acknowledged. First, in accordance with the Ministry of Education and Cultural Affairs, to maximize practicability, we have chosen a cluster (school-wise) randomization procedure, which is common and recommended in the study of school-based prevention programs [25, 69, 70]. Nevertheless, this randomization procedure differs from other studies, and especially psychotherapeutic studies, which randomize participants by subject or class. We will seek to protect the study from contamination through the randomization procedure. Randomizing at the school level ensures that participants, and particularly those from the control conditions, are unable to obtain material or information covered in the prevention condition due to contact with each other [69]. Second, we are trying to standardize the implementation of DUDE in the treatment groups through training and the manual such that high manual fidelity can be ensured. However, we are aware that in treatment group 2, teachers are unlikely to adhere to our manual 100% due to their many daily responsibilities. This will potentially have an impact on the efficacy of our program. We will attempt to monitor standardized implementation with measures of adherence (see the “Process and adherence variables” section) after each lesson, as in psychotherapy studies. However, it is not certain that this will work. It is important to determine if there are group differences between the different trainers (clinical psychologists vs. teachers) in the implementation of DUDE, as this could affect the efficacy of the program. Ultimately, the implementation of DUDE by teachers is hugely important for subsequent dissemination. Third, we must ask whether DUDE is superior to targeted prevention, because universal prevention usually achieves low effect sizes. Perhaps it would make more sense to identify pupils with high-risk or emerging self-injurious behavior using a brief questionnaire and refer them to targeted interventions that have already been shown to be effective. However, the problem with this procedure is that disclosure of psychopathological behavior in the school setting may still lead to stigmatization of affected students. Fourth, our findings must take into account the SARS-Covid-19 pandemic and its impact on pupils’ mental health. If the pandemic-related conditions that led to psychological and behavioral problems among adolescents are reversed and a “normal” daily routine is possible again, this could also lead to an improvement in mental health and be falsely associated with the efficacy of DUDE. However, the randomized controlled trial design should prevent such misconceptions, and the additional measurement of SARS-Covid-19 burdens (see the “Confounding variables” section) should control for the influence of this factor on efficacy. Nevertheless, due to the current pandemic-related high mental stress and decreased quality of life among children and adolescents, we believe it is imperative to implement universal prevention programs to improve emotion regulation and reduce maladaptive behaviors in order to help those affected and actively contribute to improving the current situation for young people.

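### The 12-month control incidence of 2.31% is a prevalence difference between age bands nominally two years apart; spread evenly over that gap, power falls from 85% to 56% (z-test) or from about 80% to about 50% (14 df)

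*Protocol article*

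**What the plan says.** All the figures are in the Sample size section of the protocol article. The planning rates are given as: "We assume an incidence rate (newly detected cases in the last 12 months) of 2.31% in the control group and 0% in the treatment group". Their source is a longitudinal study that found "a prevalence of 3% in the control group at age 12–13 years and a prevalence of 5.31% later at age 14–15 years". For the treated schools the authors hope that "no new cases will occur in the treatment group and assume a stable prevalence rate of 3"%. For the control schools they write: "In the active control group, an increase from 2.31 to 5.31% in 1 year can be assumed based on the data".

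The other inputs are 160 analysed pupils in each of eight schools per group, an intraclass correlation ("We assume an ICC of 0.015"), a two-sided unpooled z-test for cluster-randomised proportions and a 5% significance level. The section states 80% power for a difference of 2.31 points. Allowing for 20% dropout gives 200 pupils per school and 3200 in total.

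**The concern.** There are two faults in the same paragraph.

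- **Time base.** The 2.31 points accrue between two age bands that are nominally two years apart. The plan uses them as a 12-month incidence, without annualising and without saying why one year is the right interval.
- **Misquoted rise.** A rise from 2.31% to 5.31% would be 3.00 points. The source figures give a rise from 3.00% to 5.31%, which is 2.31 points. The sentence puts the difference where the starting prevalence belongs, and so contradicts the 3% given two sentences earlier.

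The second fault is one of wording and does not enter the calculation. The first does. With 0% assumed under DUDE, the control rate is the whole effect size, so any overstatement of it passes straight into the power. A reader who trusts 80% could take a non-significant result as evidence that DUDE does not work when the design had much less chance of showing a benefit.

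**Working it through.** **Inputs (Sample size section).** m = 160 pupils per school analysed, k = 8 schools per arm, ICC = 0.015, two-sided alpha 5%, p1 = 2.31%, p2 = 0%. The 12-month window used in that section is kept throughout.

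**Formulae.**
- Design effect = 1 + (m − 1) × ICC = 1 + 159 × 0.015 = 3.385.
- Effective n per arm = 8 × 160 / 3.385 = 1280 / 3.385 = 378.1.
- SE = sqrt{[p1(1 − p1) + p2(1 − p2)] / 378.1}, and λ = (p1 − p2) / SE.
- Power by z = Φ(λ − 1.960).
- Power by t: noncentral t with noncentrality λ and 16 − 2 = 14 degrees of freedom (critical value 2.145).

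**Step 1: reproduce the plan's 80%.** For 2.31% v 0%, SE = sqrt(0.0231 × 0.9769 / 378.1) = 0.00773 and λ = 2.990.
- z: Φ(2.990 − 1.960) = 84.9%.
- 14 df: 79.4% by noncentral t, or Φ(2.990 − 2.145) = 80.1% by a shifted normal.

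The stated 80% therefore reproduces with a 14-df reference, while a plain normal reference gives about 85%. Each comparison below stays within one reference. The dropout step also reproduces: 160 / 0.8 = 200 per school, and 200 × 16 = 3200.

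**Step 2: check the quoted rise.** 5.31 − 3.00 = 2.31 points, the difference used for power. 5.31 − 2.31 = 3.00 points, which is not.

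**Step 3: put the rise on a one-year basis.** The article gives age bands, not the measurement interval, so the gap is an assumption and is varied. Even accrual over the gap is also assumed. For two years, 2.31 / 2 = 1.155%, SE = sqrt(0.01155 × 0.98845 / 378.1) = 0.00549 and λ = 2.102.

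| Assumed gap | One-year control incidence | λ v 0% | Power, z | Power, noncentral t, 14 df |
|---|---|---|---|---|
| 1 year (as in the plan) | 2.31% | 2.990 | 85% | 79% |
| 1.5 years | 1.54% | 2.432 | 68% | 62% |
| 2 years | 1.155% | 2.102 | 56% | 50% |
| 3 years | 0.77% | 1.713 | 40% | 36% |

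Annualising as 1 − sqrt(1 − 0.0231) instead of halving leaves the two-year z figure at 56%.

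**Step 4: partial reductions, with 2.31% kept as the control rate.**
- 75% reduction (0.5775%): λ = 2.002, power 52% (z) or 46% (noncentral t).
- 50% reduction (1.155%): λ = 1.218, power 23% (z) or 21% (noncentral t).

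**The case against.** **The interval is not known.** The age bands would allow a gap of less or more than two years, and the cited study's own interval is not shown. This stands. A reader might infer that power is 56% and not 80%. The article does not support that as a fixed correction: the two-year gap is read from age bands, and the comparison sets a z-test figure against one that reproduces only with 14 df. The like-for-like pairs are 85% to 56%, or about 80% to about 50%. At every gap in the table longer than one year, power is below 80%.

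**A net change in prevalence is not an incidence.** If some of the 3% stop, new cases exceed the net rise. This also stands. As an illustration, a one-year incidence of about 2.03% would give 80% by the z formula. From a net rise of 1.155 points, that needs 2.03 − 1.155 = 0.875 points of stopping, or 0.875 / 3.00 = 29% of baseline cases. The article gives no rate of stopping and does not argue this way. Its treated-arm scenario, with no new cases and prevalence steady at 3%, implies none.

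**Even accrual may be wrong in either direction.** The Inclusion and exclusion criteria section says that "the first rise in incidence rates can be determined around the age of 14 years". A reader might infer that one-year incidence in this younger sample cannot exceed half of the rise. That does not follow. The same section places the highest risk of onset in these years, and the older pupils pass age 14 during follow-up.

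**The zero rate under DUDE is disclosed as a hope**, and the Limitations section concedes that "universal prevention usually achieves low effect sizes". It is an optimistic but visible assumption, not an arithmetic error. It is relevant here because it leaves no margin to absorb a lower control rate. A reader might also compare prevalences of about 4.16% and 3.00%, but the primary model is for newly detected NSSI, so power on the prevalence scale does not bear on the planned test.

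**The misquote is probably a slip** and changes no number. Agreed, but it contradicts the paragraph's own baseline and should be corrected.

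**Conclusion.** The point holds. The one-year attribution of the 2.31 points is unsupported, and the quoted starting value is wrong on the article's own figures. The stated 80% is correctly computed from its inputs (with a 14-df reference), but its main input lacks a basis.

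With a two-year gap, even accrual and complete prevention under DUDE, power is 56% by the named z-test or about 50% with 14 df, a loss of about 30 points by either method. Gaps of 1.5 to 3 years give 68% to 40% (z) or about 62% to 36% (t). These are scenarios that rest on the assumed interval and even accrual. Stopping among existing cases could raise the true incidence by an amount that the article does not allow one to estimate.

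**What to change.** In the Sample size section:

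1. Correct the control-group sentence to a rise from 3.00% to 5.31%.
2. State the interval between the two measurements in the source study.
3. Annualise the control incidence over that interval, or give the reason for keeping 2.31% as a 12-month figure (for example, evidence on new cases as distinct from net change).
4. Replace the unqualified 80% with a range computed by one named method, saying whether the reference is normal or t with 14 df. For a two-year gap this is 56% (z) or about 50% (t), with the 1.5- and 3-year values beside it.
5. Give power for partial reductions by the same method. With 2.31% in the control group, a 75% reduction has 52% and a 50% reduction 23% (z-test).

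The change is to wording and reported figures only. It adds no schools or pupils; the cost is a less favourable published power figure. It does not restore 80% power, but it lets a non-significant result be read in the light of what the design could detect.

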### Statistical analysis

The primary hypothesis will be addressed by using a univariate generalized linear mixed-effects model with logit link function for the probability of newly detected NSSI (measured dichotomously) at T3. To model the correlation within schools, schools will be included as random effects.

As secondary analyses, the generalized linear mixed model for the primary outcome will be adjusted for potential sociodemographic confounders (sex, socioeconomic status, mental stress due to the COVID-19 pandemic). In addition, we will adjust the baseline measure NSSI, although our analysis will only consider the incidence rate (newly detected NSSI in the last 12 months). Furthermore, based on the distribution of the secondary outcomes, differences in secondary outcomes between the two groups (treatment and intervention) will be compared. We will analyze emotion regulation (DERS-SF), suicidality (PSS), quality of life (KIDSCREEN-27), self-efficacy (RESE-R), general mental health (SDQ), depression (PHQ-9), and eating disorder pathology (SEED) using univariate mixed-effects models, and with non-parametric tests if necessary due to the data material.

Missing data and individuals who withdraw from the trial will be handled using an intention-to-treat (ITT) approach. All participants randomized will be considered in the analysis. In the case of dropout or missing data, we will use the multiple imputation method.

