### Primary hypothesis

Participants in the treatment group (1 or 2) receiving DUDE will show a lower occurrence of NSSI within the past 6 months at T3 compared to students in the active control group.

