### Data assessment

Data will be collected and assessed in cooperation with the Institute of Clinical Epidemiology and Biometry, University of Wuerzburg, Germany. The baseline assessment (T0) will take place after randomization and 7 days (± 3 days) before the subsequent start of the treatments. At the end of DUDE or 5 weeks after receiving the minimal intervention (± 7 days), the second measurement (T1) will be conducted. Further assessments will ensue 6 months (± 7 days; T2) and 12 months (± 7 days; T3) after the end of DUDE. After every measurement, the data will be screened for potential suicidality (see the “Emergency procedure” section). At T2, only a selection of the assessment measures will be used (see Fig. 2). We chose this procedure in order to check for iatrogenic effects which could occur immediately after the prevention [24], whereas protective effects, or rather efficacy, in universal prevention is expected later [25]. Additionally, we will evaluate how appealing DUDE is to the adolescents, as this might have an impact on the effectiveness of the program.

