#### Primary outcome

For the assessment of NSSI, we will use a modified version of the 9-item *Deliberate Self-Harm Inventory* (DSHI-9), which was used in the SEYLE study [12]. The original version of the DSHI, by Gratz, contains 17 items [30], and the DSHI-9 is an adaptation for adolescents by Lundh [31]. The modified version comprises the same facets on frequency, severity, and duration of NSSI as the 9-item version; however, self-injurious acts are combined in order to simplify and shorten the measure and to assess direct self-injury to one’s body surface only [32]. The internal consistency for the DSHI-9 lies between alpha = .66 and .85 [33].

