### Harms

In view of the non-invasive universal prevention, the risk for the participants is considered marginal. Comparable studies (i.e., SEYLE study or SOSI) showed no iatrogenic effects such as an increase in suicidality or NSSI. Irrespective of the randomization, participating pupils will benefit from a universal prevention that protects against the development of psychopathology and especially NSSI and suicidality. However, an increase in NSSI and suicidality cannot be completely ruled out. Hence, an emergency procedure has been installed in order to help conspicuous pupils (see the “Emergency procedure” section). Nevertheless, there is no obvious risk for participants. The independent Institute of Clinical Epidemiology and Biometry, University of Wuerzburg, will provide expert advice regarding all aspects of data quality. This means that the data could be checked immediately after data entry for adolescents who are potentially at risk, ensuring that the Department of Child and Adolescent Psychiatry, University Hospital of Wuerzburg, can provide them with the necessary help as quickly as possible. Beyond this, the ethics committee and the Ministry of Education and Cultural Affairs will be informed about adverse events, such as suicidal acts, and the further course of the study will then be coordinated with these entities.

The principal investigators will inform surrounding psychiatric hospitals about the study in advance. Information about where to find help as well as necessary contacts will be publicly available on the study homepage and on the information letters given to the pupils beforehand, ensuring that all participants know how to access emergency contacts. Additionally, we will provide consulting addresses and the study staff will also be available by telephone and mail. If any adolescent feels overwhelmed during the data collection or the training, another emergency protocol is in place to offer help right away. In addition, we will be in close contact with the respective educational psychologists throughout the duration of the study to ensure that psychiatric/psychotherapeutic help can be easily provided if needed.

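### The plan names an early check for iatrogenic effects and concedes that NSSI may rise, but the only NSSI comparison it describes is newly detected, dichotomised NSSI at T3

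*Protocol article*

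**What the plan says.** All references are to the protocol article.

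- **Data assessment.** The schedule was chosen "in order to check for iatrogenic effects which could occur immediately after the prevention", with protective effects expected later. T2 uses only some of the measures. Which ones is shown in Fig. 2, which is not available here.
- **Harms.** An increase in suicidality or NSSI is the article's own example of an iatrogenic effect. It then concedes: "However, an increase in NSSI and suicidality cannot be completely ruled out".
- **Statistical analysis.** The primary model is a logit mixed model "for the probability of newly detected NSSI (measured dichotomously) at T3", with school as random effect. The sentence on baseline adjustment adds: "although our analysis will only consider the incidence rate (newly detected NSSI in the last 12 months"). The secondary outcomes named are DERS-SF, PSS, KIDSCREEN-27, RESE-R, SDQ, PHQ-9 and SEED. All randomised participants are to be analysed.
- **Primary hypothesis** (likewise the Abstract and Objectives and aims). The outcome is a "lower occurrence of NSSI within the past 6 months at T3", which is not restricted to new cases.
- **Primary outcome.** The modified DSHI-9 "comprises the same facets on frequency, severity, and duration of NSSI". The Sample size section uses it in dichotomised form.
- **Inclusion and exclusion criteria.** Self-injury at T0 is not an exclusion. Only lack of consent and current individual psychotherapy are.

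**The concern.** A universal programme can do harm in two ways that a count of new cases at one year does not capture. It can raise self-injury for a time soon after delivery, and it can make self-injury more frequent or severe in pupils who already do it. The article raises the possibility of early harm itself, and its Discussion says that other universal programmes have triggered iatrogenic effects.

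A pupil with NSSI at T0 cannot become a newly detected case. Such pupils are therefore either left out of the incidence analysis, which conflicts with the statement that all randomised participants are analysed, or counted as non-events. If they are non-events, a pupil whose self-injury worsens counts the same as one who never self-injured. The data that could tell them apart, frequency and severity, enter no described comparison. Any benefit in these pupils is lost in the same way.

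At stake is whether the report could say anything about NSSI harm at the time when, and in the pupils in whom, it is most plausible.

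**Working it through.** **1. The plan's own figure.** Inputs from Sample size: 8 schools × 160 pupils = 1,280 evaluable per arm; 2.31% against 0%; ICC 0.015; two-sided 5%; unpooled z-test.

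- Design effect = 1 + (160 − 1) × 0.015 = 3.385.
- SE = √[3.385 × 0.0231 × 0.9769 / 1,280] = 0.00773.
- Power = Φ(0.0231/0.00773 − 1.96) = 84.9%.
- The stated 80% is matched by a t reference with 14 df (79.4%), or by setting the treatment rate at 0.1% instead of 0% (79.9%; the 0.1% is an assumption).
- Dropout: 160/0.80 = 200 per school, × 16 = 3,200, as stated.

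The point made here changes none of these figures.

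**2. Pupils with NSSI at T0, against expected new cases.**

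| Quantity per arm | Arithmetic | Result |
|---|---|---|
| NSSI at T0, recruited | 0.03 × 1,600 | 48 |
| NSSI at T0, evaluable | 0.03 × 1,280 | about 38 |
| New control cases | 0.0231 × 1,280 | about 30 |

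The 3% is the prevalence that the plan uses for ages 12–13. Its later-age figure of 5.31% would give 0.0531 × 1,280 ≈ 68. Removing pupils in individual psychotherapy from the analysis could lower either number.

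**3. What each wording covers.** T3 is 12 months after the end of treatment.

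| Event | Newly detected, 12 months (Statistical analysis) | Any occurrence, 6 months (Primary hypothesis) |
|---|---|---|
| New NSSI during the five-week programme | Before the window | Before the window |
| New NSSI in months 0–6 that then stops | In the window, but no rule says T1 or T2 data feed the classification | Before the window |
| New NSSI in months 6–12 | Counted | Counted |
| NSSI at T0 that persists | Not counted | Counted |
| NSSI at T0, now more frequent or severe | Not counted | Counted as an event, but the change is not seen |

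Neither wording gives a comparison at T1 or T2, and neither uses frequency or severity.

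**4. What the missing comparisons could show.**

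- *All pupils, any NSSI at one early visit.* With 3.0% in the control arm and the design effect above, 80% power needs a rise to about 7.5%. Check: SE = √[3.385 × (0.03 × 0.97 + 0.0753 × 0.9247)/1,280] = 0.0162, and 0.0453/0.0162 ≈ 2.80.
- *T0-positive pupils.* About 38 per arm is about 4.8 per school, so the design effect is 1 + 3.8 × 0.015 = 1.057. For assumed control persistence of 30%, 50% and 70%, 80% power needs 61%, 80% and 94%, that is, rises of about 24 to 31 points. With 50% in both arms, the 95% CI half-width is 1.96 × √[1.057 × (0.25 + 0.25)/38] ≈ 23 points.

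**5. Reconciling the wordings is not neutral for power.** If the primary analysis were occurrence, 5.31% against 3%, then SE = √[3.385 × (0.0531 × 0.9469 + 0.03 × 0.97)/1,280] = 0.0145. Power is Φ(0.0231/0.0145 − 1.96), about 36%.

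**The case against.** The strongest reply is that this is a condensed article. Supportive time points, subgroups and harms tables usually sit in a full protocol or SAP, and NSSI is missing from the secondary list because it is the primary outcome. The article gives no time points for any secondary outcome. The sentence limiting attention to incidence concerns covariates of the primary model and need not forbid every other NSSI summary.

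Much of this is fair, and an unseen SAP may hold such an analysis. What remains is that the article does more than stay silent. It states an aim, concedes the specific harm, and then confines its NSSI analysis to incidence. Those statements do not fit together.

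A reader might infer that early or worsening NSSI cannot be found at all. The documents do not support that:

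- The test is two-sided, so an excess of new cases under DUDE at T3 could show.
- The 12-month wording might take in early new cases.
- PSS, PHQ-9 and SDQ are compared between arms.
- The facets of the DSHI-9 are collected, and nothing says they will go unreported.
- Whether the DSHI-9 is given at T1 and T2 depends on Fig. 2.

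A reader might also infer that every T0-positive pupil lies outside the NSSI analysis. The occurrence wording, the adjustment for baseline NSSI and the commitment to analyse all randomised participants all point the other way. The article is unclear here; exclusion is not established.

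Screening after each measurement and the emergency procedure are not an answer. They are triggered by suicidality and respond to individuals; they do not compare arms.

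**Conclusion.** The point holds as a mismatch between a stated aim and the described analysis. The article announces a check for iatrogenic effects and accepts that NSSI may rise, but describes no between-arm comparison of NSSI before T3 and none of frequency or severity at any time. About 38 evaluable pupils per arm would have NSSI at T0, more than the roughly 30 new control cases expected. This assumes that the plan's 3% applies at T0 and that these pupils drop out at the general 20% rate.

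It would be tempting to apply the worldwide 17% from the Background, giving 0.17 × 1,280 ≈ 218 per arm. That rate is for adolescents generally, while the article places the peak near 16 and chose this age group to precede the rise. The plan's own input is 3%. Nor does the article set any rule by which it would declare the programme free of iatrogenic effects, so a false declaration of safety is a risk in reporting and not something the plan prescribes.

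The primary analysis and sample size are unaffected. This is a cheap improvement, and it buys a described comparison, not a decisive safety test.

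**What to change.** 1. Keep the primary endpoint. Reconcile the incidence wording (Sample size, Statistical analysis) with the occurrence wording (Abstract, Objectives and aims, Primary hypothesis): one definition, one look-back window, and a statement of how pupils with NSSI at T0 are handled. Bear in mind the 36% power if occurrence were adopted.
2. Add as secondary or safety analyses: any NSSI, DSHI-9 frequency and DSHI-9 severity, by arm, at every visit where the DSHI-9 is given (T3, and T1 and T2 if Fig. 2 schedules it). Include all pupils, with or without NSSI at T0. Use mixed models with school as random effect and the T0 DSHI-9 value as covariate.
3. Report the same quantities descriptively, with 95% confidence intervals, in pupils with NSSI at T0. State in advance that the intervals will be wide and that a null result there does not support a conclusion of no iatrogenic effect.

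The cost is analysis wording and a few extra models on data already collected. No pupils or schools are added, and no questionnaire is added where the DSHI-9 is already scheduled. The price is imprecision: a half-width of about 23 points in the T0-positive subgroup if 50% persist in each arm, which could be misread as reassurance unless item 3 is stated.

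### Secondary outcomes: the non-parametric fallback does not carry school clustering over, and the pupil's own baseline value is named as a covariate only for NSSI

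*Protocol article*

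**What the plan says.** Under Statistical analysis, the protocol article specifies a univariate logistic mixed model for NSSI at T3 and adds: "To model the correlation within schools, schools will be included as random effects". A separate secondary step then adjusts that NSSI model for sociodemographic factors, pandemic stress and baseline NSSI.

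The seven secondary scales (DERS-SF, PSS, KIDSCREEN-27, RESE-R, SDQ, PHQ-9, SEED) are to be analysed "using univariate mixed-effects models, and with non-parametric tests if necessary due to the data material". The choice depends on the observed distributions. No test, switching criterion or treatment of schools is given for the fallback, and no covariate is named for these scales.

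Under Sample size, clustering is taken seriously: "We assume an ICC of 0.015". The article says of this value that "this assumption is based on data from two studies of binge drinking behavior in adolescents". No ICC is given for any secondary scale.

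**The concern.** The mixed model's school random effect is the only device for within-school correlation that the analysis section describes. A move to a non-parametric test leaves that model behind, and nothing in the text replaces it. The usual rank tests treat pupils as independent. With whole schools randomised, that understates the variance of the arm comparison.

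The fallback may well be used for some scales. PSS (five items, three response options), SEED (six items) and PHQ-9 are given to a general school sample, and pupils in individual psychotherapy are left out of the analysis. Many scores at the floor are plausible. Objectives and aims states that the secondary outcomes will show DUDE to be superior, so a false positive there would support a declared claim.

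The second issue is precision. The article uses univariate for the NSSI model before adjustment and describes adjustment as a further step for NSSI only. The natural reading is that the secondary models are unadjusted. The Limitations section concedes that "universal prevention usually achieves low effect sizes", and only 16 schools are randomised, so precision that costs nothing should not be given up.

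**Working it through.** **Inputs from Sample size.** Two-sided 5% level, m = 160 analysed pupils per school, 8 schools per group, ICC 0.015, 2.31% v 0%, 20% dropout. The T0-T3 correlation r is not in the document; 0.5-0.6 is assumed.

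**1. The plan's own figure.** The article states: "A sample size of 160 pupils per school and eight schools per group yields a power of 80" per cent.
- Design effect: DE = 1 + (m − 1) × ICC = 1 + 159 × 0.015 = 3.385.
- Unpooled SE: √(0.0231 × 0.9769 × 3.385 / 1280) = 0.00773, so z = 0.0231 / 0.00773 = 2.99.
- Power: Φ(2.99 − 1.96) = 84.9% with normal critical values, and 79.4% with a t reference on 2 × 8 − 2 = 14 degrees of freedom.
- Recruitment: 160 / 0.8 = 200 per school, and 200 × 16 = 3200.

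The stated 80% is therefore reproduced with the t reference. The design effect is the quantity needed below.

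**2. Type I error of a pupil-level test that ignores schools.** The formula is 2 × [1 − Φ(1.96 / √DE)].

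| ICC | DE at m = 160 | Type I error |
|---|---|---|
| 0.005 | 1.795 | 14.4% |
| 0.015 | 3.385 | 28.7% |
| 0.03 | 5.770 | 41.5% |

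At ICC 0.015, the rate is 25.0% with 128 pupils per school and 32.6% with 200.

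**3. Simulation check.** 4000 trials with 16 schools, m = 160, ICC 0.015 (on the underlying normal scale) and no effect:

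| Test | Normal data | Skewed, discretised data |
|---|---|---|
| Pupil-level Mann-Whitney | 28.1% | 25.0% |
| t-test on school mean ranks | 5.4% | 5.0% |
| Exact rank test on 8 v 8 school means | 5.3% | 5.0% |

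The inflation comes from ignoring schools, not from using ranks.

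**4. Expected false positives with no true effect.** If PSS, PHQ-9 and SEED all went to an ordinary rank test, 3 × 0.287 = 0.86 would be expected, against 3 × 0.05 = 0.15. If all seven did, 7 × 0.287 = 2.0, against 0.35.

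**5. Baseline score (a separate matter from steps 2-4).**
- The variance of a school mean, in SD² units, is 0.015 between schools + 0.985 / 160 = 0.0062 within schools, 0.0212 in total. The within-school share is 0.0062 / 0.0212 = 29%.
- The chance difference between arms at T0 has SE √(2 × 0.0212 / 8) = 0.073 SD. Gaps beyond 1.96 × 0.073 = 0.14 SD arise in 5% of trials.
- If T0 explains only within-school variation, the variance falls by 0.29 × r²: 0.29 × 0.25 = 7% to 0.29 × 0.36 = 10%.
- If the correlation is equally strong between schools, it falls by r²: 25% to 36%.

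**The case against.** The article does not say that the fallback ignores schools. It names no test, and step 3 shows that cluster-aware rank methods keep the nominal level. A reader might infer that the plan as written has a 29% false-positive rate on its secondary outcomes. The text does not support that: the first-line method is a mixed model, to which the figure does not apply, and the ICC behind it was borrowed from binge drinking for NSSI.

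Nor does the article say that T0 scores are excluded. That is read from its use of univariate and from adjustment being described only for NSSI. Test names and covariate lists are often left to a fuller document.

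Three further inferences fail:
- **All seven scales are skewed symptom scores.** KIDSCREEN-27 measures quality of life and RESE-R self-efficacy. No distributions are reported, and skew alone seldom rules out a mixed model with about 1280 pupils per arm.
- **Chance baseline gaps match the expected effects.** No expected effect is given for any secondary scale, and the remark on low effect sizes carries no number. Chance imbalance is also already reflected in the unadjusted standard error, so it is a matter of precision.
- **Omitting T0 contributes to the 29%.** It plays no part in it.

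These objections limit the claim but do not remove it. The article goes beyond silence: it writes in a data-dependent move away from the only analysis that it ties to school clustering, and it places baseline adjustment with one outcome only.

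**Conclusion.** The concern holds in conditional form. The fallback for the secondary outcomes is badly fixed: it depends on the data, has no named test or trigger, and has nothing that keeps the school structure. If an ordinary pupil-level rank test filled the gap, its type I error would be about 29% at ICC 0.015 and 160 pupils per school (25% in the skewed simulation). Across assumed ICCs of 0.005 to 0.03 it would be about 14% to 41%. The size rests on the choice of test and on an ICC that the document does not give for these scales.

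Not naming the T0 score as a covariate is a lesser matter of lost precision. The variance reduction available is about 7-10% at the cautious end and up to 25-36% at the favourable end, for an assumed correlation of 0.5-0.6. The upper range also needs that correlation to hold between schools. The primary analysis is untouched. The point should be corrected before analysis.

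**What to change.** For each secondary scale, state a mixed model at T3 with arm, the pupil's own T0 score and a school random effect. State the rule for leaving that model before outcome data are seen. Restrict any fallback to a method that respects randomisation by school, for example a school-level permutation test on baseline-adjusted school means or an ordinal mixed model with a school random effect. These are examples; other cluster-aware methods would also serve. If an ordinary pupil-level rank test is what was intended, it should be ruled out explicitly.

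The cost is wording only. T0 scores are already collected, and pupils without one can be covered by the multiple imputation already planned. Sample size, schedule and the primary analysis do not change.
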